### 2.2. Secondary Objective:

The secondary objectives are to evaluate:

- a. the rate of HBsAg loss and anti-HBs serconversion,
- b. To establish predictive markers at baseline and during the first 12 weeks of treatment for response of primary and secondary endpoints:

serologic markers

HBsAg levels

immunologic markers

T cell responses, cytokine production of T cells.

histologic markers

HAI (histology activity index)

Fibrosis grade

HBsAg level

cccDNA level (liver)

HBV-DNA level (liver)

biochemical markers (livertransaminases)

ALT

AST

LDH

AF

yGT

virologic markers

HBsAg level

cccDNA (plasma)

HBV-DNA level

HDV co-infections

Hostgenomics

DNA and RNA expression levels in PBMC's, liver

Proteomics

Possible protein candidates include: SR-B1(CD36), CD81, certain Claudins, STAT-1 and 2, ApoE and more

Inflammatory markers

CRP, neopterin

Neoplastic markers

Rate of development of hepatocellular carcinoma

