## 9 STATISTICAL ANALYSIS

### 9.1 Descriptive statistics

The main efficacy variable in the comparison of treatments A and B to treatment C ( no treatment) is the proportion of subjects in each treatment group achieving loss of HBsAg. The primary objective is to demonstrate superior efficacy of treatment A and/or B to treatment C.

The sample sizes were calculated as follows:

Per treatment group 44 per group (88 for both groups) is needed to achieve 81% power to detect a difference between the two treatment groups and the control group. The proportion in the PEG/IFN and adefovir group is assumed to be 0.01 under the null hypothesis and 0.20 under the alternative hypothesis. The proportion in the control group (no treatment) is 0.01. The statistical test used is the two-sided Fisher's Exact test . The significance level of the test was targeted at 0.05. A group sample of 44 persons in the control group is needed to achieve a 81% power to detect a difference between the PEG/IFN adefovir or PEG/IFN tenofovir.

Regarding a 10% drop-out due to peginterferon side-effects or other reasons a total of 50 patients are needed in each group.

Univariate logistic regression analyses will be performed to identify predictors of response to the combination therapy of PEGASYS® and ADF dipivoxil (Hepsera®) and PEGASYS® and tenofovir. Significant predictors from the univariate analysis will be combined into a multivariate logistic regression analysis. As a rule of thumb, the number of potential predictors to be included in a multivariate analysis should not exceed the number of responders (or non-responders, whichever is the lowest) divided by 10. With 100 patients included, the maximum number of predictors in a multivariate analysis is five, assuming a response rate of 0.50. Initially, the number of significant predictors from univariate analysis to be included in the multivariate analysis will be restricted following multi colinearity diagnostics. If the number of potential predictors remains too large however, a bootstrap procedure will be followed drawing 200 samples of the same size as the original (n=100) with replacement, each time repeating the multivariate logistic regression analysis. Descriptives of this bootstrap procedure will be reported to identify a stable predictor set. The level of significance during all these analyses is set at 0.05.

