- (e) Eye examination will be done on indication. Any patient complaining of decrease or loss of vision must have a prompt and complete eye examination. Patients with preexisting ophthalmologic disorders (eg, diabetic or hypertensive retinopathy) should receive periodic ophthalmologic exams during Peg-IFN therapy. Peg-IFN treatment should be discontinued in patients who develop new or worsening ophthalmologic disorders.
- (f) non-invasive measurement of the liver to detect fibrosis and cirrhosis
- (g) Only for patients with decreased kidney function. If there are clinically significant laboratory abnormalities, repeat no less frequently than every 2 weeks or as clinically indicated, with appropriate toxicity management, until they return to normal or baseline values. Urinalysis to be performed via dipstick, with subsequent microscopic evaluation if positive for hemoglobin at the discretion of the investigator.
- (h) Only for certain patients at risk, don't repeat if data from previous assessments are available
- (i) Roche TaqMan®; when HBV DNA is more than the maximal detection limit, ten or hundred time dilution is proceeded.
- (j) Paxgene TM DNA sample (tube) will be collected. The DNA samples will be used exclusively for exploratory DNA research (genotyping of hostgenomics) to evaluate drug disposition genes.(e.g. metabolic enzymes and drug transporters), to explore possible underlying genetic variants involved in therapy response in HBV chronically infected. Samples will only be processed in a number of subjects. No other testing will be performed on these samples.
- (k) Paxgene TM RNA sample (tube) will be collected to assess the expression of RNA in peripheral blood using whole genome microarray technology. These samples are collected as part of an effort to better understand the effects of medication. Samples will only be processed in a number of subjects. No other testing will be performed on these samples.
- (l) plasma tube will be collected for proteomics profiling. These samples are collected as part of a study to better understand the effects of medication on liver activity. Samples will only be processed in a number of subjects. No other testing will be performed on these samples. Possible protein candidates include: SR-B1(CD36), CD81, certain Claudins, STAT-1 and 2, ApoE and more.
- (m) During the study a quality of life index according to SF36 standardized questionnaires will be administered

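### Section 9.1 sets one unadjusted 0.05 level for all predictor analyses and gives no other method for the genomic and proteomic markers listed in objective 2.2b

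*Protocol*

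**What the plan says.** Protocol section 2.2, item b, aims to establish markers, at baseline and in the first 12 weeks of treatment, that predict response on the primary and secondary endpoints. Beside serologic, immunologic, histologic, biochemical, virologic and inflammatory markers it lists host genomics, "DNA and RNA expression levels in PBMC's, liver", and a proteomics class whose candidate list is left open. Section 7.1.2 repeats this as a secondary endpoint.

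Footnote (k) to the Schedule of Assessments in the Appendix says that RNA samples are taken "to assess the expression of RNA in peripheral blood using whole genome microarray technology". The schedule places these samples at baseline, week 4 and week 12 within the 12-week predictor window, and again later.

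Section 9.1 gives the analysis:

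- Screen: "Univariate logistic regression analyses will be performed to identify predictors of response to the combination therapy".
- Selection: "Significant predictors from the univariate analysis will be combined into a multivariate logistic regression analysis".
- Cap of one predictor per ten responders: "With 100 patients included, the maximum number of predictors in a multivariate analysis is five, assuming a response rate of 0.50".
- Collinearity: the number carried forward "will be restricted following multi colinearity diagnostics".
- If too many candidates remain, "a bootstrap procedure will be followed drawing 200 samples of the same size as the original (n=100) with replacement", refitting the multivariable regression each time.
- Level: "The level of significance during all these analyses is set at 0.05".

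The protocol describes no other analysis for the genomic, RNA or proteomic markers.

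**The concern.** A 0.05 screen lets through one in twenty null markers. With a short list of plausible clinical predictors that is tolerable. With an array it yields hundreds of nominally significant markers, and the rule then sends all of them on as candidates for a model with room for only a few. Real predictors would have to compete with noise for those places.

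The Introduction says predictors are wanted to guide therapeutic interventions, so a marker wrongly reported as predictive has a practical cost. Section 9.1 also states the level outright. An analysis plan that added an adjustment would be departing from the protocol, not filling a gap in it.

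**Working it through.** **Inputs.** Level 0.05 and the screening rule: section 9.1. Treated patients: 100 (section 9.1). Planned response under treatment: 0.20 (sections 4.4 and 9.1). Candidate markers: section 2.2b. RNA platform and sampling times: Appendix schedule and footnote (k). The array size is not given; 10,000 to 20,000 transcripts is assumed.

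**1. The plan's own figure.** Cap = N × min(p, 1−p) / 10 = 100 × 0.50 / 10 = 5, as stated. At the planning response of 0.20 it is 100 × 0.20 / 10 = 2. That mismatch is a separate matter; here it shows only how few places there are.

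**2. Counting the named markers.** Counting HBsAg in serum once and leaving out the hepatocellular carcinoma rate:

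| Class | Markers |
|---|---|
| Serologic | 1 |
| Immunologic | 2 |
| Histologic | 5 |
| Biochemical | 5 |
| Other virologic | 3 |
| Inflammatory | 2 |
| Subtotal | 18 |
| Named proteins (claudins as one, STAT-1 and STAT-2 separately) | 6 |
| Total | 24 |

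**3. Chance findings from the screen.** With m null markers, the expected number is 0.05 × m. The chance of at least one, if the markers are independent, is 1 − 0.95^m.

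| m | Expected | At least one |
|---|---|---|
| 18 | 0.9 | 60% |
| 24 | 1.2 | 71% |
| 10,000 (assumed) | 500 | about 100% |
| 20,000 (assumed) | 1,000 | about 100% |

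These are for one time point and one response definition.

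**4. Share of significant markers that are false.** With a fraction f of true predictors and power w, the share is 0.05(1−f) / [0.05(1−f) + w·f]. Simulated power for a univariate logistic regression with N = 100 and 20% response is 31% at an odds ratio of 1.5 per SD, 73% at 2 and 96% at 3. Across that range of odds ratios:

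| f | False share |
|---|---|
| 1% | 84–94% |
| 5% | 50–75% |
| 10% | 32–59% |
| 20% | 17–39% |

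The false share passes one half when f is below 0.05 / (0.05 + w): about 5% at full power and about 14% at 30% power. That is plausible for an array. It is not shown for a short list of markers chosen on prior grounds.

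**5. Do the built-in restraints help?**

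- The cap limits how many predictors enter the model, not which ones pass the screen.
- The collinearity step removes overlapping markers. Independent noise markers pass it.
- The bootstrap runs only if too many candidates remain, and it resamples the multivariable fit on markers already selected from the same data. In a simulation with 24 pure-noise markers, 100 patients and 20 responders, markers that had passed the 0.05 screen were significant in a median of about 60% of the 200 resamples, and about three quarters of them in more than half. Used this way, the bootstrap can make noise look stable.

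**The case against.** The strongest reply is that section 9.1 never names the arrays, the genotyping or the proteomics. Its procedure suits a short list with complete data: a rule-of-thumb cap, collinearity diagnostics and a bootstrap with n = 100. Footnotes (j), (k) and (l) say samples will be processed in only some subjects, which fits poorly with resampling all 100. Footnote (j) calls the DNA work exploratory, and (k) and (l) tie the RNA and plasma samples to understanding medication effects. A reader might infer that the protocol expressly orders a 0.05 logistic screen of the whole genome. It does not. That reading joins objective 2.2b to a level set for all the predictor analyses, so the point has to be conditional.

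A reader might also infer that most markers called predictive would be false. The documents do not support that overall, because they give neither the number of tests nor the share of true predictors. For the named markers about one chance finding is expected even if all are null. The Introduction gives reason to think at least one is not: in the sponsor's study in patients with high viral load, low baseline HBsAg had a positive predictive value of 85% for HBsAg loss. Several listed markers are also related, such as the liver enzymes, so the 71%, which assumes independence, probably overstates the chance of at least one false positive.

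Finally, an unadjusted level is common in secondary predictor searches. That holds for the short list. It does not answer the point for the high-dimensional classes, which 2.2b lists as candidate predictors and for which no other method is stated. Only the DNA work is labelled exploratory.

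**Conclusion.** The point stands in conditional form. The protocol fixes one unadjusted 0.05 level for its only predictor method, while objective 2.2b includes high-dimensional marker classes. If those classes are screened by that method, chance findings would dominate them, at about 500 to 1,000 per time point. That size rests on the assumed number of transcripts and on nearly all of them being null. For the 24 named markers the expected number is about 1.2 if all are null, which is modest.

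None of the three restraints in 9.1 controls the error made at the univariate screen. This concerns a secondary objective and leaves the comparison of the treated groups with the control group untouched. It is worth correcting, because the level is stated and the change is cheap.

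**What to change.** Amend section 9.1 in three places:

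1. Restrict the 0.05 logistic screen to a short pre-named set of clinical and virologic predictors, led by baseline HBsAg level, sized to the number of responders expected.
2. For the genomic, RNA and proteomic families, use false discovery rate control within each family (for example Benjamini-Hochberg) and report the results as hypothesis-generating, as footnote (j) already implies for DNA.
3. Repeat the whole selection, including the univariate screen, inside each bootstrap sample.

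The cost is plan wording and some programming, with no new data, visits or patients. The downside is that fewer weak markers will be called significant. A Bonferroni rule would cost more than is needed: in the simulations at 20% response, power for an odds ratio of 2 per SD falls from about 73% at 0.05 to about 23% at 0.002, roughly the Bonferroni level for 24 markers (0.05 / 24 = 0.0021). At 0.05 / 20,000 = 0.0000025 it is about zero.

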## **9.2 .Interim analysis**

After inclusion of 50,100 and 150 patients and yearly during longterm follow-up an interim analysis will be performed by the investigator. The statistical test is the two-sided Fisher's exact test. Stopping rules for the study are the occurrence of serious adverse events.

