## 2. OBJECTIVES

### 2.1 Primary Objective:

The primary objective is to demonstrate the efficacy of combination therapy (Peg-IFN and adefovir or Peg-IFN and tenofovir) for inducing loss of HBsAg compared to no-treatment in HBeAg negative chronic hepatitis B patients with low viral load. HBsAg loss is defined as HBsAg level < 0.05 IU/mL.

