### **11.4 End of study report**

The investigator will notify the accredited METC of the end of the study within a period of 8 weeks. The end of the study is defined as the last patient's last visit.

In case the study is ended prematurely, the investigator will notify the accredited METC, including the reasons for the premature termination.

Within one year after the end of the study (end of short term follow-up after 72 weeks), the investigator/sponsor will submit a final study report with the results of the study, including any publications/abstracts of the study, to the accredited METC.

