### **11.5 Public disclosure and publication policy**

After interim analysis and yearly during long term follow up (5 years) the results of this study will be presented and published.

In accordance with generally recognized principles of scientific collaboration, co-authorship with any company personnel will be discussed and mutually agreed upon before submission of a manuscript to a publisher.

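### HBsAg loss has no assessment week and none of the planned looks is named primary, so no single result answers the primary objective

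*Protocol*

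**What the plan says.** Section 2.1 gives the whole endpoint definition: "HBsAg loss is defined as HBsAg level < 0.05 IU/mL". Section 7.1.1 repeats it. Section 9.1 makes the main efficacy variable the proportion per group with loss. None of the three names a week. The schedule of assessments measures HBsAg at every visit from screening to week 72 and then yearly for five years.

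For the sizing, section 9.1 states "The statistical test used is the two-sided Fisher's Exact test" and "The significance level of the test was targeted at 0.05", with assumed proportions of 0.20 and 0.01. Success means superiority of either or both combinations over no treatment.

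Section 9.2 sets the looks: "After inclusion of 50,100 and 150 patients and yearly during longterm follow-up an interim analysis will be performed by the investigator". It adds "The statistical test is the two-sided Fisher's exact test", and its only stopping rule is serious adverse events. It gives no significance level, boundary or variable, and does not say which look is primary. Section 11.5 adds: "After interim analysis and yearly during long term follow up (5 years) the results of this study will be presented and published".

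Week 72 appears in section 11.4 as the "end of short term follow-up after 72 weeks", which dates the final study report and not the primary analysis.

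**The concern.** An endpoint that can be read at any of some 20 visits over 72 weeks, and then at five yearly visits, is not one endpoint. Looks triggered by inclusion or by calendar year mix patients with very different follow-up, and the protocol ranks none of them above the others. If they disagree, it does not say which one answers the primary objective.

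Time matters here on the protocol's own figures. The Introduction cites spontaneous loss of 1-2% per year in Western patients. For HBeAg-negative patients given Peg-IFN-based therapy for one year, it cites about 4% loss with one year of treatment and 12% five years after treatment. A control rate of 0.01 with no time attached therefore fits some readings of the endpoint and not others.

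The looks at 50, 100 and 150 inclusions also come before most patients have an outcome. No efficacy stopping rule uses them, yet the investigator of an open-label trial with untreated controls runs them, and section 11.5 lets results be published.

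**Working it through.** **1. The plan's own figure.** Inputs from section 9.1: 44 per group, 0.20 against 0.01, two-sided Fisher's exact test at 0.05. Power is the sum of Bin(x; 44, 0.20) × Bin(y; 44, 0.01) over all pairs (x, y) with Fisher p ≤ 0.05. Result: 0.806, against the stated 81%. The figure reproduces.

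**2. What the missing week does to the sizing.** Spontaneous loss of h = 1% or 2% per year is from the Introduction. Cumulative control loss at time T is 1 − exp(−hT). The treated rate is held at 0.20 and 44 per group are kept.

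| Assessment time | T (years) | Control loss, h = 1% / 2% | Exact power, h = 1% / 2% |
|---|---|---|---|
| Week 48 | 48/52 = 0.92 | 0.9% / 1.8% | 81% / 73% |
| Week 72 | 72/52 = 1.38 | 1.4% / 2.7% | 77% / 65% |
| Week 72 plus 5 years | 6.38 | 6.2% / 12.0% | 38% / 11% |

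The treated rate would also change with time, so the last row is not a forecast. It shows that the stated power belongs to an assessment at about one year with loss at the low end of the cited range.

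**3. Maturity of the inclusion looks.** The protocol gives no accrual period, so uniform accrual over A months is an assumption. At inclusion of patient n, patient i has been followed for A(n − i)/150 months.

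| Accrual | With week-48 data at 50 / 100 / 150 | With week-72 data at 50 / 100 / 150 |
|---|---|---|
| 12 months | 0 / 0 / 11 | 0 / 0 / 0 |
| 24 months | 0 / 30 / 80 | 0 / 0 / 46 |
| 36 months | 3 / 53 / 103 | 0 / 30 / 80 |

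Even if all of the first 50 patients had a complete outcome, 16 or 17 per arm would give an exact power of 17.5% or 20.9% at 0.20 against 0.01.

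**4. False-positive chance.** Simulation with no treatment effect:
- 50 per arm, 24-month uniform accrual, the same constant loss hazard in all arms, no dropout.
- Every included patient counted at each look, with cumulative loss.
- Two-sided Fisher p ≤ 0.05 for either combination against control.
- Nine looks: the eight in section 9.2 plus one when the last patient reaches week 72. The yearly looks start one year after that.

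| | 1% per year | 2% per year |
|---|---|---|
| Any rejection, nine looks | about 4% | about 9% |
| Rejection favouring a treatment | about 2% | about 4.5% |
| Three inclusion looks alone | at most 0.1% | about 0.1% |
| One test at each patient's own week 72 (exact) | 0.01% | 0.2% |

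Nearly all of the growth comes from the yearly looks. Fisher's test rejects very rarely when there are few events: at 0.01 in both arms with 50 per arm, one comparison has a size of about 0.00001.

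**The case against.** Several points on the other side stand.

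- **What is tested in 9.2.** The section names neither variable nor level, and an unseen SAP may hold an adjustment. That the looks test HBsAg loss is inferred: Fisher's exact test is specified elsewhere only for that comparison. A reader might conclude that the plan commits to unadjusted primary-outcome tests at 0.05. The protocol does not say that; it states 0.05 once and no other level.
- **Size of the inflation.** A reader might apply the textbook figures for repeated testing at 0.05: 17.6% for eight looks, or 30% with two comparisons sharing a control. They do not apply at these event rates. At the cited 1-2% per year, false claims of superiority stay below 5% over all nine looks. The inclusion looks add next to nothing, and the yearly looks fall after the week-72 reporting point.
- **Week 72 is not already fixed.** It rests on a reporting clause. The precedent in the Introduction, 23% loss, was seen after one year of therapy, which points at least equally to week 48.
- **Bias and publication.** HBsAg is a quantitative assay on centrally processed frozen samples, which limits assessment bias. Section 11.5 does not clearly require arm-level publication at 50 and 100 inclusions. Effects on enrolment, retention or controls starting treatment are plausible, but nothing in the protocol demonstrates them.

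None of this supplies an assessment week or a primary look. The definition of the primary endpoint is a protocol matter, not SAP detail.

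**Conclusion.** The point holds because of the missing assessment week and the absence of a named primary analysis. Followed as written, the protocol yields several competing answers to its primary objective, and its 81% power cannot be tied to any of them. The inclusion-triggered looks would carry little outcome data: under an assumed 24-month accrual, none of the first 100 patients and about 46 of 150 would have reached week 72 at their looks.

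Error inflation is a secondary consequence and modest in size: about 4% to 9% for any rejection and about 2% to 4.5% in favour of treatment, at 1% and 2% loss per year. These figures assume 24-month accrual, equal constant hazards, nine looks each tested at 0.05, and HBsAg loss as the variable tested in section 9.2. They do not support describing the trial as having a grossly inflated error rate.

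**What to change.** - **Sections 2.1, 7.1.1 and 9.1:** name one assessment week for HBsAg below 0.05 IU/mL. Week 48 matches the one-year rate behind the sizing; week 72 is the end of short-term follow-up. Confirm in sections 4.4 and 9.1 that 20% and 1% are the expected rates at that week. Test once, when the last randomised patient reaches it.
- **Section 9.2:** limit the looks at 50, 100 and 150 inclusions to safety, with no between-arm efficacy test. Report the other of weeks 48 and 72, and the yearly follow-up, as estimates with confidence intervals.
- **Section 11.5:** allow no arm-level efficacy publication before the primary analysis.

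The cost is amendment wording and a later first efficacy publication. If the confirmed control rate at the chosen week is above 1%, the sample size needs another look, as the power table shows.
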